#### Data sharing

Data and study-generated statistical code will be shared beyond the study investigators with an executed data use agreement. Study-generated intervention materials will be shared freely with the community via a website after the study results are published.

#### Dissemination policy

Authors will include investigators participating in the study procedures, analysis, and manuscript writing. Professional writers will not be used.

#### Data safety and monitoring

To ensure confidentiality, each participant is assigned a code number. All interviews and SCKnowIQ data are coded with the code number and linked to the participant’s name in order to display tailored intervention with the participant’s name. The participant’s name is removed from the database when statistical analyses are conducted. The demographic information and other self-report outcomes will be entered at a secure web site on a secure application server with data written to a secure database server that is maintained by the UF Health Sciences information technology (UF IT) group. No data remain, even temporarily, on the computer used by the participant. Access to the database server is restricted to the lead statistician and the principal investigator (as backup) and the programmer. The two servers (application and database) are backed-up nightly, and there is fire- and water-secure, offsite storage of backups. The UF IT systems are highly controlled to minimize privacy or data breaches. All applications undergo a stringent security and privacy evaluation before being deployed on the IT managed severs.

## Discussion

Our study, the first of its type, has a strong scientific premise with many strengths to achieve the aims. With the exception of one recent study [22], there are virtually no other studies except ours [14–17] published to date about young adults with SCD or SCT and their intentions to become parents. Our study is significant in addressing this need. We have a strong rigorous study design that builds on our prior studies and includes a longitudinal, randomized, repeated measures clinical trial with follow-up of knowledge and behavior for 2 years. This longitudinal design is needed to boost the intervention sufficiently to support concordant behavior and to allow participants sufficient time to engage in the behaviors needed to implement the parenting plan and then for us to measure behavior endpoints. A well-known theoretical framework, Kolb’s ELT and nudges toward concordant behavior, guide our study. The research team is diverse, interdisciplinary, and exceptionally well qualified with expertise in SCD, cultural competence, strong engagement with community-based organizations that can facilitate recruitment, RCT design, methods and analyses, multimedia nudges, and targeted and tailored computerized interventions. Retention strategies are strong and will likely yield low attrition rates as in our past studies. The intervention is exceptionally innovative and provides both targeted (to group characteristics) and tailored (to individual responses) messages. Fidelity of intervention delivery is rigorous. Study instruments have acceptable psychometrics. Data analyses are well planned and take advantage of current approaches to repeated measures and missing data. If CHOICES produces successful concordant behavior in *at-risk* individuals with SCD or SCT, extension to studies with adolescent populations and international populations where millions of children are born annually will be warranted.

Although there are common challenges to building trustworthy relationships with participants from underrepresented minority groups, we have had success in doing so with a sample of young adults with SCD and SCT, more than 90% of whom are Black or African American. Our diverse team (5 Black, 3 Asian, 1 Latina, and 4 White) has experience in conducting research with the population and are continually mindful of respectful, genuine, and reciprocal approaches that foster and maintain trust. As in any study of health behavior, there is the possibility that self-reporting on the items may be under reported because of the personal nature of the items. We have the cultural expertise of several team members as well as a strong team of co-investigators, collaborators, advisors, and staff members, all of whom know the population and will vigilantly assist us to maintain our mindfulness of the cultural context of the participants.

We considered a health promotion intervention as an attention control condition rather than usual care. The e-Book is not “usual care” for individuals with SCT recruited from the community since they typically do not receive any genetic counseling under usual care. Hence, the e-Book provides new information for them. Even though our prior findings show that there were knowledge gains in the e-Book condition, which could diminish the group differences for the primary endpoint, we decided to retain the e-Book. We did so because our retention rate was high in the preliminary study, and it is not clear that a health promotion intervention not focused at all on SCD or SCT would exhibit comparable retention. Also, from an ethical perspective, we decided that the e-Book information on SCD/SCT should be available to all *at-risk* for their child inheriting SCD.

We considered randomization by State, instead of by individuals, as we did for the recently completed pilot study to avoid contamination that is possible if participants from the same state encounter each other and share information about their intervention. This type of contamination could lead to an underestimation of the intervention effect. However, our interviews of participants found that the interaction between participants from the same state was negligible. In addition, we observed substantial differences in characteristics of participants from different regions. Our experience, therefore, led to our decision to randomize at the individual level for the current RCT, because any potential loss of power due to the small risk and effect of contamination will be greatly outweighed by the large gain in study power of individual randomization over cluster randomization with substantial differences between clusters. Self-report of reproductive health behaviors, which includes but is more than sexual activity, may not reflect actual sexual activity and is a limitation of the proposed study. We have taken steps to facilitate accurate capture of reproductive behavior, including use of online data capture, which is known for reduced reporting bias for sensitive information than an interview format [23]. We also used standard questions when possible, to reduce reporting bias.

Study findings will provide important evidence for primary prevention of the unbelievable suffering and the enormously high cost of healthcare associated with this inherited rare but lethal blood disorder. As a genetic counseling follow-up model, CHOICES may translate into informed parental decisions and preparedness for the consequences of their preconception decisions and reduced uninformed inheritance of single-gene diseases such as SCD. Considering the implications for SCD globally, the potential impact is enormous.

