One of every 500 African Americans has SCD, and one of every 12 African Americans has SCT [1]. SCT is usually asymptomatic but, as an autosomal recessive condition, persons with SCT are at risk for having children with SCD if their reproductive partners have SCT or SCD. A rough estimation based on prevalence of SCT and SCD shows that if no action is taken, 0.94 in 500 births among African Americans will exhibit SCD, very close to the reported statistic of 1 in 500 births. Thus, these rates suggest that the *at-risk* population is not currently engaged in systematic efforts to reduce the risk of their children inheriting SCD, an important scientific premise for the proposed study. If both reproductive partners have SCD, for each pregnancy, there is 100% chance of the child having SCD. If one partner has SCD and one has SCT or another hemoglobinopathy, for each pregnancy, there is 50% chance of the child having SCD. If both partners have SCT, for each pregnancy, there is 25% chance of the child having SCD. If only one partner has SCD or SCT and the other partner has normal hemoglobin (Hb A), for each pregnancy, there is 0% chance the child will have SCD. Examples of two behaviors needed for a person with SCD or SCT to reduce the risk of having a child with SCD include [1] talking with one’s potential reproductive partner about sickle cell status and [2] seeking partners with Hb A. These behaviors, however, are not well-known or easy to accomplish for them or for any of the other 3 million Americans with one of the 10,000 other single-gene diseases (e.g., Huntington disease, Fragile X syndrome, cystic fibrosis, or muscular dystrophy) [13]. Study findings will provide evidence on how to mitigate uninformed inheritance of SCD worldwide and serve as an intervention model in follow-up to genetic counseling for other single-gene disorders.

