### Eligibility criteria

Participants are eligible to participate in the CHOICES study if they meet the following eligibility criteria: Confirmed diagnosis of SCD, SCT, or another hemoglobinopathy, able and intends to conceive a child, wants to avoid the risk of having a child with SCD, are able to speak and read English, are at risk for having a child with SCD, and are between the ages of 18–45 years.

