### Randomization

Randomization to e-Book and CHOICES groups will be stratified by SCD and SCT to assure that each group is balanced on this variable. Within each stratum, permuted block randomization with a block size of four will be performed to ensure group balance. The statistician will conduct the randomization and the programmer will implement it via computer code. All other team members will be blind to the group assignment with no access to the electronic group assignment table within the software application.

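### No rule covers two partners who both enrol, so a couple who share one at-risk-time outcome can be split between arms, and the contamination argument does not address this

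*Protocol article*

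**What the plan says.** Under Eligibility criteria, participants must be people who "are at risk for having a child with SCD"; they must also intend to conceive and wish to avoid that outcome. The Introduction explains what creates the risk: "persons with SCT are at risk for having children with SCD if their reproductive partners have SCT or SCD".

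Under Randomization, "Randomization to e-Book and CHOICES groups will be stratified by SCD and SCT", and "Within each stratum, permuted block randomization with a block size of four will be performed". SCD/SCT status is the only stratification factor. The article gives no rule that links partners, excludes a second partner or assigns partners together.

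The Discussion says that state-level randomization, used in the pilot, was considered again because participants from one state might share material. It concedes that such contamination would make the effect look smaller than it is. It then reports that "our interviews of participants found that the interaction between participants from the same state was negligible". Together with the regional differences seen in the pilot, this "led to our decision to randomize at the individual level for the current RCT".

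Two further places matter. The Intervention section says that CHOICES trains participants to talk to their partner and to work out the couple's joint risk. The section on at-risk time builds the outcome from the partner's sickle cell status, contraception, assisted reproduction, pregnancy, prenatal testing and pregnancy outcome.

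**The concern.** The contamination argument considers contact between participants who happen to live in the same state. It does not consider the closest contact that this sample could contain, which is two members of one couple. If a participant with SCT is at risk because the partner is known to carry SCT or SCD, that partner has the qualifying diagnosis and is at risk as well. The partner may also meet the age, language and intention criteria. Recruitment through families, churches, clinics and social networks makes joint enrolment plausible.

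If such a couple is split, two things follow. A CHOICES participant who does what the program teaches passes its content to a control participant. The two partners also report mostly the same reproductive events, so the couple shows little or no arm difference in at-risk time. Both effects pull the estimate toward zero. The behaviour calculation has no reserve to absorb this.

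**Working it through.** **Inputs from Sample power.** At-risk time is 30% ± 37% (CHOICES) and 41% ± 44% (e-Book). Knowledge is 12.0 ± 3.0 and 11.1 ± 3.1. N = 430, taken as 215 per arm, with two-sided alpha 0.05. Stated power is 80% for at-risk time and 85% for knowledge.

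**Step 1: reproduce the plan's figures.**
- At-risk time: SE = √((37² + 44²)/215) = √(3305/215) = 3.92 points. 11/3.92 = 2.81, and power = Φ(2.81 − 1.96) = 80.1%. The stated 80% is reproduced, and exactly 430 completers are needed for it.
- Knowledge: SE = √((3.0² + 3.1²)/215) = 0.294. 0.9/0.294 = 3.06, and power = 86.4%, close to the stated 85%.

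**Step 2: chance that a couple is split (s).** If the partners fall in different strata or different blocks, their assignments are independent and s = 1/2. If they fall in the same block of four, three slots remain after the first partner is placed and two of them belong to the other arm, so s = 2/3. These are the two ends of the range.

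**Step 3: dilution.** Let f be the share of participants whose partner is also enrolled. The article does not give f, so the values below are assumptions. If a split couple contributes no arm difference, the expected difference is 11 × (1 − f·s). This is the worst case within a split couple.

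| f (assumed) | Share in split couples, s = 1/2 to 2/3 | Expected difference (points) | Power, at-risk time | Completers for 80% at s = 1/2 |
|---|---|---|---|---|
| 0 | 0 | 11.0 | 80.1% | 430 |
| 5% | 2.5–3.3% | 10.7–10.6 | 78.1–77.4% | 452 |
| 10% | 5.0–6.7% | 10.45–10.27 | 76.0–74.5% | 476 |
| 20% | 10.0–13.3% | 9.9–9.5 | 71.4–68.1% | 530 |

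Worked line: f = 10% and s = 1/2 give 11 × 0.95 = 10.45; 10.45/3.92 = 2.67; Φ(2.67 − 1.96) = 76.0%.

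**Step 4: knowledge.** If split partners shared all information, power at s = 1/2 would fall from 86.4% to 82.8% (f = 10%) or 78.6% (f = 20%). If they shared half, it would be 84.7% or 82.8%. Knowledge is tested person by person, so full sharing is again an extreme.

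**Step 5: check by simulation.** I simulated 430 participants assigned at random in equal numbers, with outcomes fully shared within couples, and compared the arms by t-test (6,000 runs each). Power was 77% at f = 10% and 71% at f = 20%, with mean differences of 10.5 and 9.9 points. With no true effect, the rejection rate was 4.95% and 4.6%, so Type I error is not inflated.

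**The case against.** The strongest objection is that the frequency of couples is unknown and may be small. A reader might infer that selecting at-risk people makes almost every participant's partner an eligible carrier. The article does not support that. Its scoring rule for at-risk time treats anyone without a protective behaviour as at risk, which can include people with no partner or a partner of unknown status. For a partner of unknown status, the Introduction's prevalences give a carrier chance of only about 1/12 + 1/500 = 8.5%. A partner must also meet the other criteria and upload a record of status. This part of the objection stands, and it is why the point is limited to partners whose status is known.

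The interviews are also not empty of information. Couples living together are participants from the same state, so frequent joint enrolment should have shown up as interaction. That stands as weak evidence that couples were uncommon in the pilot. It does not show what happens when a couple is split, because a design randomized by state hardly allowed that. A reader might add that the pilot sample was half not at risk. The article says this of an earlier recruited group and does not identify that group with the state-randomized pilot, so the point does not rest on it.

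A reader might also expect couples in the same arm to make the standard error too small. They do not do so here. Same-arm couples add positive covariance and split couples add negative covariance. The two offset at s = 1/2, and the test becomes conservative at s = 2/3.

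Zero difference within a split couple is a worst case as well. Having a partner with normal hemoglobin is specific to the person, and partners can change over 24 months.

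Finally, the full protocol may contain a partner rule. That is possible. But the article makes the contamination argument in full and fixes the unit of randomization on it without mentioning this route.

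**Conclusion.** The point holds as a cheap improvement, not as an error that undermines the trial. The evidence offered against contamination does not reach couples split between arms, and the article states no rule that prevents them. The consequence is dilution toward the null, mainly of the secondary endpoint. Power for at-risk time would be about 77–78%, 75–76% or 68–71% instead of 80% if 5%, 10% or 20% of participants had an enrolled partner. These figures assume a split probability of 1/2 to 2/3 and no difference within split couples. The couple share is an assumption throughout. At the low end the loss is slight. The primary knowledge endpoint is less exposed, and false positives are not a concern.

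**What to change.** Add one screening question: is your current partner enrolled in this study or applying to it? Admit only the first partner of a couple to the randomized Aim 1 sample, and state this rule under Eligibility criteria and Randomization. Amend the Discussion so that the contamination argument covers partners as well as participants from the same state.

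The rule has to act before randomization. Dropping one partner at analysis would leave the other partner's exposure and shared events in the data.

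The cost is small. Staff already telephone every applicant and check a health record before randomization, and the demographic questionnaire already records the partner's SCT status. The downside is the loss of a few otherwise eligible second partners. If couples are rare, almost nobody is lost. The gain in power from individual over state-level randomization is kept.
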